**Table 12.2. Estimated power for specific aim 2 assuming 300 evaluable subjects in each group during the first year.**

| Normative rate of pregnancy loss | Reduction from intervention |     |
|----------------------------------|------------------------------------|-----|
|                                  | 33%                                | 50% |

### 12.5 Data management

Data entry and storage will be conducted on-site. All completed forms (source documents) are checked for completeness before the participant leaves the ward or clinic by a nurse other than the nurse who initially completed the forms. After ensuring no questions are left blank, the forms are accumulated and sent to the data entry office at the end of each day. Data clerks using FoxPro programs will double enter all forms. The Data Manager will run verification programs and SAS frequencies to check for errors and out of range entries. After all data entry has been completed, the forms are archived in numeric order in locked cabinets in the data entry office. In addition to local data management and analysis, the data will electronically be transferred to Baltimore for further management and analysis.

### 12.6 Data analysis.

Analyses will be done using an intention to treat approach. Separate analyses for HIV infected and uninfected women will be performed and the effect of the intervention on outcomes in these two groups will be compared. The effect of the intervention will be based on comparing incidence of BV and portion of pregnancy losses between treated and untreated (control) subjects.

Multiple hypotheses will be tested in this study, requiring a diverse array of analytical methods to compare the treatment and control arms. Descriptive comparisons will be made between the two study groups to identify potential confounding variables which could bias hypothesis testing through direct comparisons. When possible, as differences are noted, multivariate adjustment methods will be used to minimize the effect of confounders on testing the hypotheses. Continuous variables will be tested for skewness, kurtosis and outliers which could cause imprecision in standard asymptotic statistical methods. When such conditions occur, transformations such as logarithms, dichotomization or Winsorizing will be used, or nonparametric statistical methods will be implemented. For the statistical tests described below, both P-values and confidence intervals will be calculated for the parameters of interest.

---

 Although we use the term incidence in the text, it is more accurate to define this measure as cross-sectional prevalence because the number of BV cases during a 3 month interval are a combination of new and continuing cases (due to incomplete cure and recurrences).

Most outcomes of interest (e.g., presence of BV) are uncensored binary or categorical events. These include demographic and specific behavioral factors, etc. Contingency (n x 2) tables will be used to compare these events between the two study arms. Adjustment for covariates will be made with logistic regression. Comparison of binary events between two time-points within the same group will be done using methods that match on the same individual such as discordant pairs or conditional logistic regression. In other outcomes of interest which are continuous comparison of mean values will be made using t-tests. Adjustments for covariates will be performed through linear regressions. Comparisons of continuous covariates for the same individuals in a group over different time periods will be made using paired z-tests and linear regressions on differences of values.

Some outcomes will be censored binary events. Standard survival analysis techniques such as Kaplan-Meier curves and Poisson regression will be used to directly compare outcome in both groups. These methods can also compare incidence rates within the same group over different time periods. Multivariate analogues that utilize covariates (proportional hazards models and Poisson regression) will adjust these comparisons for other covariates.

For some analyses we will pool repeated measurements from the same individual over multiple study visits. For example, occurrence of BV across all post-intervention study visits will be compared between study groups. For these analyses, generalized estimation equation models, which use an individual as cluster unit, will be fit to obtain robust covariance. For binary outcomes, a logit link will be used.

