**D. 2. h. Other laboratory tests.** A vaginal wet mount will be examined microscopically at each visit to detect motile trichomonads and candida albicans (hyphae and buds). Wet mount examination to detect trichomonads is not highly sensitive; therefore, vaginal swabs will be archived, and PCR or culture will be considered. These tests, however, are expensive and are not performed locally in Malawi. Overgrowth of candida is a possibility with use of intravaginal antibiotics (1). We will test for candida at each visit. We will not routinely test all women for gonococcal or chlamydial infections because the rates are low (see Table 7 for prevalence of gonorrhea). A recent N-9 pilot study found chlamydia in less than 1% among women of reproductive age at two sites in Malawi. Maternal and infant hemoglobin will be performed using a finger or heel prick blood spot by a portable (Hemocue) machine. The hemoglobin results will be immediately available.

**D.2. i. Management of STD and BV cases.** As we indicated earlier, women (and their partners) with syphilis will be provided treatment at no cost. We will follow the Malawi recommendations and provide syndromic treatment for other STDs. Treatment of BV is not included in this WHO recommended approach of syndromic management. Women with discharge, however, are either treated for trichomonas infection (using oral metronidazole) or for vulvovaginal candida infection. Since oral metronidazole might influence rates of BV, details of treatment (type of drug, dose and duration) will be documented at each visit on a case report form. We will not deny a participant any medication recommended by a clinician. The data analysis will take into account concomitant medications.

**D. 2. j. Physical and anthropometric examination.** Trained nurse-midwives will perform physical examinations of the mother at each visit based on structured procedures documented in the manual of operations. Standard scales for measurement of weight and height will be used. The staff will be trained and adequately supervised, and machines will be regularly recalibrated.

**D. 2. k. Study questionnaires.** Trained interviewers and nurse midwives will complete structured questionnaires. A baseline demographic and clinical questionnaire will be completed at enrollment and updated at follow-up visits. A delivery examination form will be completed before discharge of

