For some analyses we will pool repeated measurements from the same individual over multiple study visits. For example, occurrence of BV across all post-intervention study visits will be compared between study groups. For these analyses, generalized estimation equation models, which use an individual as cluster unit, will be fit to obtain robust covariance. For binary outcomes, a logit link will be used.

Data monitoring and reporting. This trial will be monitored by a Data and Safety Monitoring Board (DSMB). Formal interim analyses of efficacy of the intervention, based on the primary endpoints, will then be performed at approximately six month intervals during the projected study duration. Recommendations for early termination of positive or negative results will be guided by the symmetric group sequential O'Brien-Fleming Boundary (58). The O'Brien-Fleming design allows for early termination if extreme initial results are seen, while essentially allowing employment of the standard single stage one-sided 0.025-level test statistic at the final analysis if it is reached. This enables one to maintain the power of the single-stage design in the presence of interim monitoring without having to increase the maximum sample size. As has been the plan for other clinical trials conducted by our research team in Malawi, we will arrange for regular dissemination of information.

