## 5.7 Enrollment procedures

Each woman enrolling in the METRO study is systematically assigned to next available ID. For example, if the first HIV negative woman is assigned ID 11001, the next HIV negative woman should be assigned ID 11002. Similarly, if the first HIV positive woman is assigned ID 12001, the next HIV positive woman should be assigned ID 12002.

Each clinic will receive two separate lists of IDs; one list of IDs for randomization of women who are HIV negative, and another list of IDs for randomization of HIV positive women. See listing below for each clinic::

| Clinic | Code | ID Range HIV -ve | ID Range HIV+ve |
|---------------|-------------|-------------------------|------------------------|
| QECH          | 1           | 11001-11500             | 12001-12500            |
| Limbe         | 2           | 21001-21500             | 22001-22500            |
| Cholomoni     | 3           | 31001-31500             | 32001-32500            |
| Zingwangwa    | 6           | 61001-61500             | 62100-62500            |
| Ndirande      | 7           | 71001-71500             | 72001-72500            |

Within these ID ranges assigned to each clinic, women are randomized to receive either the active product or placebo.

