#### 12.3.1 Instructions for using the allocation study ID's

##### By Whom

Study coordinator (as the rest of the study investigators and workers, the study coordinator is completely blinded about the treatment assignment).

Procedure

1. Assign these Lists to the five Study Clinics as shown in section 12.3. above
2. Each woman enrolling in the study will be sequentially assigned the next available ID in each clinic.

12.4 Sample size and analysis plan12.4.1 Sample size and power:

The following design specifications will apply: number of treatment groups: 2; follow-up period: approximately one year; hypotheses will be tested using a one-sided type 1 error of  $\alpha=0.05$ . Unless stated otherwise, powers are obtained based on Fisher's exact test for comparisons of proportions in two groups.

We will recruit 1664 women of whom 832 will be HIV infected and 832 will be uninfected. In each group of women, 416 will be randomized to treatment arm and 416 to placebo arm. Based on previous experience in Malawi, losses due to dropouts and non-compliance will be less than 10% per year. Thus at least 375 women in each arm will return to each study visit during the first year.

Primary endpoint: effect of treatment on BV incidence. Power estimates for this primary endpoint are shown in Tables 12.1. In previous studies from Malawi, cross sectional prevalence of BV among untreated women was 30% and that of any vaginal disturbance was 89%.

**Table 12.1. Estimated power for specific aim 1 (comparing BV at each visit during the first study year assuming at least 375 evaluable study subjects in each group).**

| Normative rate
in untreated women | Reduction from intervention |       |
|--------------------------------------|------------------------------------|-------|
|                                      | 33%                                | 50%   |
| 0.30                                 | .87                         | ~1.00 |
| 0.89                                 | ~1.00                       | ~1.00 |

Thus there will be **0.87** and almost **1.00** power to detect 33% reductions in cross sectional visit prevalence of BV (normative rate 0.30 in untreated subjects) and any vaginal flora disturbance (normative rate .89 in untreated subjects).

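### Covariates are chosen from observed differences between arms, and drugs given after randomisation are to be taken into account, despite the intention-to-treat rule

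*Protocol*

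**What the plan says.** Section 12.6 of the Manual of Operations, and the same text in Section D.4 of the research plan, sets the covariate rule in two steps. First, "Descriptive comparisons will be made between the two study groups to identify potential confounding variables which could bias hypothesis testing through direct comparisons". Then, where possible and "as differences are noted, multivariate adjustment methods will be used to minimize the effect of confounders on testing the hypotheses". No covariate, threshold or fixed model is named, and the comparison is not limited to baseline variables. Logistic regression is the stated adjustment method for binary outcomes, and a GEE model pools BV over visits. The same sections declare an intention-to-treat approach and separate analyses in HIV-infected and uninfected women.

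Section D.2.i says that women with discharge are treated either for trichomonas, with oral metronidazole, or for candida. It warns that oral metronidazole might influence BV rates, has all such treatment recorded at every visit, and concludes: "The data analysis will take into account concomitant medications". It does not say how.

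Two pieces of baseline information are available and not used by rule. Every woman is tested for vaginal flora disturbance at the first visit (Section D.1; visit schedule in Section 3.2). Randomisation is run within clinic and HIV status: "Each clinic will receive two separate lists of IDs" (Section 5.7), one for each HIV group.

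**The concern.** In a masked randomised trial, differences between arms at baseline arise by chance. They are not confounding in the sense in which 12.6 uses the word. A rule that adjusts for whatever differs lets the data decide which model produces the treatment effect. The wording leaves open what counts as a difference, which variables are examined and which result is primary. Section D.4 also plans efficacy looks about every six months, so the covariate set could differ from one look to the next.

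The medication sentence raises a separate problem. Treatment for discharge starts after randomisation, and increased discharge is one of the four clinical criteria for BV (Section D.2.f). The protocol gives reasons why the gel might change that trigger: it may reduce trichomonas (Significance section) and genitourinary symptoms (D.6), and candida overgrowth is possible with it (D.2.h). If the gel changes who receives oral metronidazole, then adjusting for the drug, or excluding users, compares women selected by a consequence of treatment. That is no longer the intention-to-treat comparison.

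**Working it through.** **1. The plan's own power figure.** Inputs from Section 12.4.1: "416 will be randomized to treatment arm and 416 to placebo arm" in each HIV group; 416 × 0.9 = 374.4, taken as 375 evaluable per arm; control BV 0.30; 33% reduction, so 0.30 × 0.67 = 0.201; and "powers are obtained based on Fisher's exact test for comparisons of proportions in two groups". Exact enumeration of Fisher's test, with 0.201 and with 0.20 in the treated arm:

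| One-sided alpha | Power at 0.201 | Power at 0.20 |
|---|---|---|
| 0.05 | 0.921 | 0.926 |
| 0.025 | 0.865 | 0.872 |

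The stated 0.87 is reproduced at 0.025. Section 12.4.1 says that "hypotheses will be tested using a one-sided type 1 error of" 0.05, while D.4 refers to the "standard single stage one-sided 0.025-level test statistic at the final analysis". Those two statements need reconciling separately. What matters here is that 0.87 belongs to an unadjusted test.

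**2. What fixed adjustment for baseline BV would add.** The documents give no baseline-to-follow-up association, so it is assumed: baseline BV prevalence 0.30, and an odds ratio of 1, 2, 4 or 8 between baseline and follow-up BV (correlation 0, 0.15, 0.30, 0.45). Logistic regression was simulated for one HIV group at one visit, 375 per arm, 0.30 against 0.201, with 10,000 trials per setting:

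| Assumed OR | Unadjusted, 0.025 | Adjusted, 0.025 | Adjust only if imbalance p<0.05, 0.025 | Unadjusted, 0.05 | Adjusted, 0.05 |
|---|---|---|---|---|---|
| 1 | 0.880 | 0.882 | 0.880 | 0.931 | 0.930 |
| 2 | 0.888 | 0.896 | 0.889 | 0.939 | 0.944 |
| 4 | 0.885 | 0.908 | 0.888 | 0.937 | 0.952 |
| 8 | 0.876 | 0.933 | 0.885 | 0.932 | 0.965 |

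The gain runs from about 0 to 6 points at 0.025 (0.933 − 0.876 = 0.057 at most) and from about 0 to 3 points at 0.05. Adjusting only when an imbalance is seen recovers little of it.

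**3. Type I error.** Same simulation with no treatment effect. The Monte Carlo standard error is √(0.05 × 0.95 / 10,000) ≈ 0.002 at nominal 0.05.

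| Assumed OR | Fixed rule (adjust if p<0.05), nominal 0.05 | Better of two, nominal 0.05 | Fixed rule, nominal 0.025 | Better of two, nominal 0.025 |
|---|---|---|---|---|
| 1 | 0.047 | 0.048 | 0.025 | 0.025 |
| 2 | 0.051 | 0.059 | 0.026 | 0.030 |
| 4 | 0.052 | 0.065 | 0.027 | 0.035 |
| 8 | 0.049 | 0.071 | 0.022 | 0.037 |

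A mechanical rule holds its level. Freedom to take the better of the adjusted and unadjusted results does not, even with one candidate covariate.

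**4. Taking later medication into account.** This illustration uses 1,000,000 women per arm and wholly assumed inputs. An unmeasured tendency to BV raises both discharge and visit BV; discharge leads to oral metronidazole with probability 0.5 or 0.9 (0.05 without discharge); the gel has no direct effect on visit BV.

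- Gel does not change discharge: intention-to-treat, adjusted and user-excluded odds ratios are all 0.99 to 1.00. There is no bias.
- Gel changes discharge (log odds −2, −1 or +1) and the drug has no effect on BV: the intention-to-treat odds ratio is 1.00, adjusting for the drug gives 0.89 to 1.16, and excluding users gives 0.89 to 1.20.
- Gel changes discharge and the drug does reduce BV (log odds −1.2): the intention-to-treat odds ratio is 0.86 to 1.23, because it includes the effect through the drug. Adjusting gives 0.89 to 1.17, which does not recover the direct effect of 1.00 either.

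**The case against.** The other side has four good arguments.

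First, a reader might infer that the randomisation strata are ignored altogether. They are not. Section 12.6 analyses the two HIV groups separately, and 12.4.1 sizes the trial within each. That conditions fully on HIV status, and a pooled primary model with an HIV term would conflict with the design. Only clinic is unused.

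Second, a reader might infer that the trial is underpowered for lack of adjustment, or that choosing covariates by imbalance inflates error. Neither is supported. The 0.87 is for an unadjusted test, so a possible gain is forgone and nothing planned is lost. A fixed imbalance rule keeps its level; the risk lies in the discretion that the wording leaves.

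Third, taking medication into account could mean no more than tabulating it or running a sensitivity analysis, and 12.6 does not repeat the sentence. Bias also needs the gel to change who is treated, which the documents make plausible but do not show. Table 4's 14.12 trichomoniasis detections per 100 person-visits is not a rate of metronidazole use, so it does not size the treated group. This stands as a limit on the claim. It does not remove the problem, because the sentence is a commitment about the analysis with no stated boundary, alongside an intention-to-treat declaration.

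Fourth, a statistical analysis plan that is not shown might name first-visit BV and clinic. Their absence from the protocol would not be a finding by itself. The finding is that the protocol states a contrary, data-driven rule, which such a plan would have to override.

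**Conclusion.** The point holds in a limited form. The covariate rule in 12.6 and D.4 is data-driven and open to discretion, and the D.2.i sentence sits badly with intention to treat.

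The sizes are modest and conditional:

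- **Precision:** about 0 to 6 points of power forgone at 30% BV and one-sided 0.025, resting on an assumed baseline odds ratio of 1 to 8.
- **Error rate:** up to 0.037 (nominal 0.025) or 0.071 (nominal 0.05) for one covariate, and only if the more favourable analysis is chosen.
- **Medication:** 0.89 to 1.16 around a true odds ratio of 1.00 when the drug is adjusted for, under assumed inputs, and nothing if the gel leaves drug use unchanged.

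The documents do not show how BV varies by clinic, so no figure can be put on leaving clinic out. The change is worth making because it is nearly free.

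**What to change.** In 12.6 and D.4, replace the two covariate sentences by: *Within each HIV group, the primary BV model includes treatment, V1 BV status and clinic; no covariate is chosen from observed differences between arms.* Report a standardised risk difference from this model.

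In D.2.i, replace the last sentence by: *The primary analysis does not adjust for or exclude on medication started after randomisation; its use is reported by arm, and any analysis accounting for it is a sensitivity analysis.*

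The cost is wording. First-visit BV, clinic and concomitant medication are already recorded. At the planned rates, one visit in one HIV group gives about 375 × 0.30 + 375 × 0.201 ≈ 188 BV cases for six coefficients besides the intercept (treatment, V1 BV and four for the five clinics), so the model is easily supported. The one small drawback is that the adjusted odds ratio is conditional on the covariates; the standardised risk difference deals with that.

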#### 12.7 Data monitoring

This trial is monitored by a local Data and Safety Monitoring Board (DSMB). The members of the DSMB have no vested interest in this study. An initial administrative/safety analysis will be performed after the first three months of accrual. This will be followed by formal analyses of safety and efficacy of the intervention, based on the primary endpoints. Rates of accrual, retention, adherence and adverse events will be closely monitored and presented to the DSMB.

#### 12.8 Blinding rules

This is a double-masked clinical trial. Blinding of study participants will remain in place until the study is completed (after all data have been entered into the study database and all queries have been settled). However, unblinding can be considered if the clinician providing service decides that it is necessary to know the exact treatment the client has been receiving. Under such circumstances, the Field Director will contact the PI to arrange with the study statistician to make this information available. Participants will be informed of their treatment assignment only at the study completion. To preserve the integrity of the study, participants who are terminated early (e.g., for having completed the study visits schedule) will wait until every woman has been enrolled and completed the study.

### 13.0 ADDENDUMS

#### 13.1 Study population

Women who have been screened for HIV in other studies such as the HIVNET 016A condom promotion and Mastitis studies are eligible for enrollment. Likewise, women of reproductive age who are sexually active (e.g., women attending family planning clinics, postnatal and under-five clinics) are also eligible as long as they agree to be HIV tested. All prospective participants should not be pregnant. This modification opens enrollment to all women who satisfy inclusion criteria. The study is not restricted to postnatal women.

#### 13.2 Screening consent form

A new consent form has been developed and added to this study forms to obtain consent for HIV testing. This is intended only for women who were not tested previously. This HIV screening process will precede enrollment. The enrollment consent form will be separately completed on all women.

